## Abstract

**Background:**

In recent decades, several studies have shown changes in the intestinal microflora among patients with rheumatoid arthritis (RA). Therapeutic measures using probiotics have shown favorable effects on the recovery of these patients. However, most studies have used probiotic supplements. In this study, we aimed to investigate the effect of probiotic cheese consumption on inflammatory and anti-inflammatory factors, disease severity, and symptoms in these patients.

**Methods:**

This study is a randomized, double-blind clinical trial, in which forty patients with mild to moderate severity of RA will be randomly allocated to receive either 30 g/day probiotic cheese (*n* = 20) or only low-salt and low-fat cheese without any added probiotic (*n* = 20) for 12 weeks. Assessment of anthropometric measures and biochemical indicators, including serum concentrations of high-sensitivity C-reactive protein (hs-CRP), tumor necrosis factor-α (TNF-α), interleukin-6 (IL-6), and interleukin-10 (IL-10), will be done at the study baseline and end of the trial. In addition, disease severity and disability will be assessed by DAS-28 and the HAQ-DI questionnaire, respectively.

**Discussion:**

Diet is the leading environmental factor affecting the gut microbiota. A prebiotic-rich diet and probiotics might be beneficial in this regard. To the best of our knowledge, the effect of probiotic supplements on inflammation in these patients has widely been assessed; however, there is only one study that examined the effect of probiotic-containing food in these patients. Further studies are needed to investigate the effect of probiotic-containing foods on inflammatory markers and symptoms in patients with RA.

**Trial registration:**

Iranian Registry of Clinical Trials IRCT20201120049449N1. Registered on 14 February 2021

## Background

Rheumatoid arthritis (RA) is an inflammatory autoimmune condition that can lead to cartilage and bone destruction and eventually joint deformities. It affects 0.5 to 1% of the world’s population [1] and is more common in women than in men [2]. The prevalence of this condition in Iranian adults was 0.33% [3].

Several factors are involved in the onset and progression of RA, but the exact physiopathology is yet unknown. In addition to genetics, several environmental factors, including diet, smoking, alcohol consumption, have been studied in this regard. Nutritional interventions along with medications, physiotherapy, and regular exercise have been applied in the management of RA [4–7]. The imbalanced intestinal microbiota has also recently gained significant attention in this regard. The disturbance in the gut microbiota might alter the immune function through elevating pro-inflammatory factors, which can, in turn, exacerbate the severity of RA [8–10]. Numerous interventions have used probiotic supplements in the prevention and treatment of RA. Findings from these investigations have revealed a favorable effect of probiotic supplements on inflammatory and anti-inflammatory cytokines in these patients [11, 12].

However, probiotic supplementation, in which a high dose of probiotics is given to patients, might endanger the patients’ health [13]. Widespread and unregulated administration of probiotics, especially in persons who have a weak immune system, can result in infection, sepsis, metabolic disturbances, and immunological defects [13]. In addition, probiotic supplements are expensive, and given that most RA patients have low socioeconomic status and expend on other medications as well, administration of probiotic supplements to these patients would impose a further cost to these individuals. Therefore, it is essential to find an appropriate approach to carry probiotics into the body without these problems. Earlier studies have shown that probiotic-rich foods are effective in cooling down inflammation as strong as supplements [14–16]. Consumption of probiotic foods has several benefits, including taking probiotics in more controlled dosages. In addition, maintaining the consumption of these foods in routine life is more accessible than taking probiotic supplements for a loge time. Despite several studies about the effect of probiotic supplementation on inflammatory symptoms in patients with RA, we are aware of only one study that examined the effect of probiotic foods in these patients. In a clinical trial conducted on patients with RA, Nenonem et al. examined the effect of uncooked Lactobacilli-rich fermented wheat drink for 8 or 12 weeks. They found that this probiotic diet decrease symptoms of rheumatoid arthritis. However, the dose of probiotics in these foods was uncertain in that study, and they chose an uncommon food to carry probiotics into the body. Furthermore, they examined the effect of this intervention on high-sensitivity C-reactive protein (hs-CRP) only [17]. Therefore, this randomized, placebo-controlled, parallel clinical trial was designed to investigate the effect of probiotic cheese consumption on inflammatory, anti-inflammatory, disease activity, and severity factors in patients with rheumatoid arthritis.

## Methods/design

### Participants

This study is a parallel superiority randomized clinical trial, with a 1:1 allocation ratio which will be done in 2021, in which participants will be recruited from Shariati Hospital, Tehran, Iran. Women who will meet the criteria will be included in the current study: (1) those aged 20–60 years, (2) have a body mass index (BMI) of 25–40 kg/m^2^, and (3) those who have been diagnosed with a mild to moderate RA. RA will be diagnosed by a rheumatologist using the American College of Rheumatology (ACR) criteria. Disease Activity Score-28 (DAS-28) > 3.2 will be considered as mild to moderate RA [18, 19]. Patients whose conventional medications (methotrexate, prednisolone, hydroxychloroquine, sulfasalazine) were not changed in terms of type or dosage over the past month will be included. Individuals with (1) other inflammatory diseases including pancreatitis and inflammatory bowel disease (IBD), (2) acute heart disease or kidney and liver disease, (3) gastrointestinal disorders or lactose intolerance, (4) those who are pregnant or lactating, and (5) those who were using antibiotics, pre-biotic or probiotic supplements, multi-vitamin, and mineral supplements during the last 3 months will not be included. The study would be restricted to non-smokers and non-alcoholic individuals. People who are routinely using probiotic-enriched foods in their usual diet will not be included as well. The exclusion criteria would be any alteration in the type or dosage of medicines during the intervention, taking dietary supplements or antibiotics, smoking and alcohol use throughout the study, and getting pregnant. We will also exclude patients who fasted the whole day during the study, as Muslims do during Ramadan. All participants will provide informed written consent. Moreover, the study protocol has been recorded on the IRCT website (IRCT20201120049449N1). The flow diagram of the project is shown in Fig. 1.

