### Adverse events

We will ask the patients to report any adverse events that may have occurred during the study. These events will be recorded by investigators. If a given trial participant will complain about any rare harmful effect of the intervention or will want to quit the study based on personal reasons, we will exclude her/him from our trial.

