### Statistical analysis

Statistical analyses of all data will be performed using the SPSS software version 21.0 (SPSS Inc., Chicago, IL, USA). To handle non-adherence, we will use the intention-to-treat approach for data analysis. Missing values will be dealt with using the last observation carried forward (LOCF) method. Data will be expressed as mean ± standard deviations (± SD) and percentages. The one-sample Kolmogorov–Smirnov test will be used for assessing the normality of the distribution of data. In the case of a non-normal distribution of a variable, we will apply the log transformation. If the variables were non-normally distributed even after log transformation, we would use non-parametric tests in the analyses. Continuous variables will be compared between the two groups by independent samples *t*-test (or its non-parametric equivalent). We will apply the chi-square test to examine the distribution of participants in terms of categorical variables. To find the effect of the intervention on outcome variables, repeated measures analysis of variance (or its non-parametric equivalent) will be used. In these analyses, the effect of the intervention, time, and time-intervention interaction will be explored. The potential difference in baseline levels of outcome variables as well as differences in dietary intakes and physical activity levels, if any, between the two groups will be controlled for in these analyses. *P* values will be considered significant if they were < 0.05.

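### Exclusions for events after randomisation are not reconciled with the intention-to-treat statement, so the hs-CRP comparison can be biased whether excluded patients are deleted or carried forward

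*Protocol article*

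**What the plan says.** The Participants section of the protocol article first gives the entry restrictions. It then gives a separate list of events that can only happen once a patient is in the trial: "The exclusion criteria would be any alteration in the type or dosage of medicines during the intervention, taking dietary supplements or antibiotics", followed by "smoking and alcohol use throughout the study, and getting pregnant". Fasting is added: "We will also exclude patients who fasted the whole day during the study, as Muslims do during Ramadan".

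The Adverse events section extends the list to harm complaints and personal reasons for leaving; its wording for such a participant is: "complain about any rare harmful effect of the intervention or will want to quit the study based on personal reasons, we will exclude her/him". The same section says of reported adverse events: "These events will be recorded by investigators".

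The Statistical analysis section states: "To handle non-adherence, we will use the intention-to-treat approach for data analysis". It deals with missing values by LOCF. According to the Study design and intervention section, primary and secondary outcomes are measured at baseline and at the end of the 12 weeks, with no visit in between.

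No section says whether an excluded patient still has the week-12 assessment or stays in the analysis set.

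**The concern.** Intention-to-treat protects the randomised comparison only if patients are analysed as assigned, whatever happens to them afterwards. Here the article offers it as a remedy for non-adherence, while two other sections take randomised patients out for things that occur during follow-up.

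Some of these triggers can be linked to outcome or arm. Patients enter with DAS-28 above 3.2, so their disease is active and a medicine change may follow a flare. Antibiotics usually follow an infection. A harm complaint may be a consequence of the assigned cheese. If such patients leave, the two groups compared at week 12 are no longer the groups that were randomised. Blinding does not prevent this, because the biological effect of the assigned cheese can itself drive the event.

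At stake is the primary hs-CRP comparison in a trial of 20 per arm, where each patient is 5% of an arm. Week-12 values that were never collected cannot be recovered later.

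**Working it through.** **Step 1. Put the sections side by side.**

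| Section | What it does |
|---|---|
| Participants | Excludes for medicine change, supplements, antibiotics, smoking, alcohol, pregnancy or whole-day fasting during the study |
| Adverse events | Excludes for a harmful effect or a wish to quit; records reported events |
| Statistical analysis | Intention-to-treat for non-adherence; LOCF for missing values |
| Study design and intervention | Outcomes at baseline and end of trial only |

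Two readings are possible. (a) Excluded patients are deleted from the analysis. (b) They leave the study and LOCF fills in week 12. Under (b) the only earlier observation is baseline, so the imputed change is exactly zero.

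**Step 2. Reproduce the plan's figure.** Inputs from the sample size section: difference 5.71, SD 5.93, z values 1.96 and 0.85.

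n = 2 × (1.96 + 0.85)² × 5.93² / 5.71² = 17.03, stated as 17 per group. The figure reproduces. The planned effect is 5.71 / 5.93 = 0.963 SD.

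**Step 3. Illustrate the bias.** Assumptions that are not in the documents:
- The hs-CRP change Y is normal with SD 1, mean 0 in control and −0.963 in intervention.
- A flare score S = 0.6·Y + 0.8·noise has SD 1 and correlation 0.6 with outcome.
- A patient is excluded if S exceeds a cut c.

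For arm mean μ, let b = c − 0.6μ, and let φ and Φ be the standard normal density and distribution function.
- Proportion excluded = 1 − Φ(b)
- Mean among those kept, m = μ − 0.6·φ(b)/Φ(b)
- Mean with baseline carried forward = Φ(b)·m

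Cut c = 1.0:
- Control: b = 1.000, excluded 15.9%, m = −0.173, carried forward −0.145.
- Intervention: b = 1.578, excluded 5.7%, m = −1.036, carried forward −0.977.
- Difference: 0.86 SD with deletion, 0.83 SD carried forward.

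Cut c = 0.5:
- Control: b = 0.500, excluded 30.9%, m = −0.306, carried forward −0.211.
- Intervention: b = 1.078, excluded 14.1%, m = −1.119, carried forward −0.962.
- Difference: 0.81 SD with deletion, 0.75 SD carried forward.

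Against 0.963 SD, deletion understates the effect by about 10% and 16%, and carrying baseline forward by about 14% and 22%.

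**Step 4. Check that the direction is not fixed.** Suppose there is no true effect and only the 10% of intervention patients with the worst change leave. The upper 10% point is 1.282 and φ(1.282) = 0.1755. Deletion then gives a spurious benefit of 5.93 × 0.1755 / 0.9 = 1.16 hs-CRP units, or 0.6 × 1.16 = 0.69 if exclusion correlates only 0.6 with outcome. So the same rule can dilute a real effect or create a false one, depending on who is removed.

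**The case against.** The best defence is that *exclude* means withdrawal from participation, not deletion. LOCF has work to do only if patients without a week-12 value stay in the analysis, so the pairing with intention-to-treat is coherent. That stands as a possible reading, and a reader who infers that the two statements cannot both hold goes further than the text allows. It does not remove the problem. The article does not say which reading applies, and under this one a patient who flared or was harmed is scored as unchanged.

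A reader might also infer that harms are hidden. The documents do not support that: reported adverse events are recorded, and the auditing section sends unpredicted risks to the steering and ethics committees. What may be lost is the later follow-up and outcome data of a patient who reported harm.

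Not every trigger is plausibly tied to outcome. The fasting example is Ramadan, which has no evident link to arm or flare, and nothing in the article ties supplement use to outcome. The Background's infection warning concerns high-dose or unregulated supplementation and is given as a reason for preferring food, so it is not evidence of harm from this cheese.

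Finally, the illustration rests on assumed rates. The heavier pattern averages about 22% excluded, above the plan's 20% drop-out, and attributes every exclusion to flare. The shift under deletion, 0.10 to 0.15 SD, is one third to one half of the standard error with 20 per arm, √(2/20) = 0.316 SD. These points limit the size claimed, not the existence of the gap.

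**Conclusion.** The concern holds in this form: the post-randomisation exclusions in the Participants and Adverse events sections are not reconciled with the intention-to-treat statement, and the primary hs-CRP comparison can be biased under either reading of *exclude*. Medicine change, antibiotics and harm complaints are the triggers that matter most.

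The document gives only an overall 20% drop-out, so neither the size nor the direction of the bias can be derived from it. The range of 0.86 to 0.75 SD against a true 0.96 SD is conditional on the assumed exclusion rates, the 0.6 correlation and a control mean change of zero. That carrying baseline forward does worse than deletion is also specific to those assumptions.

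This should be settled before the data are analysed, and preferably before any patient is excluded, because an uncollected week-12 measurement cannot be restored.

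**What to change.** Reconcile the Participants, Adverse events and Statistical analysis sections, and state four things:

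1. The primary analysis set is all randomised patients, in the group to which they were assigned.
2. Week-12 hs-CRP and adverse-event follow-up are sought from every randomised patient who has not withdrawn consent, whatever event occurred. A patient who wishes to leave cannot be bound by this.
3. The list of events in the Participants section serves only to define a secondary per-protocol set.
4. The Adverse events section says that a patient reporting harm is recorded and, with consent, followed to week 12, so that the report alone does not end data collection.

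This concerns follow-up and analysis only. It proposes no rule on medicines, antibiotics, fasting or stopping the study cheese.

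The cost is protocol wording and a few week-12 visits for patients who would otherwise be dropped. The downside is that the primary effect then includes patients whose background medication changed; the per-protocol analysis can show the result without them.

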**Fig. 1 Fig1:**
[figure not shown]
Diagram of the study design

### Study design and intervention

The diagram for Standard Protocol Items: Recommendations for Interventional Trials (SPIRIT) is shown in Fig. 2. After recruiting participants, they will be stratified based on age (20 to < 40 and 40–60 years), BMI (< 30 and ≥ 30 kg/m^2^), and type of medicines (nonsteroidal anti-inflammatory drugs (NSAIDs)/disease-modifying antirheumatic drugs (DMARDs)/steroids/immunosuppressive) into different blocks and then will be randomly allocated to the intervention or control groups. For each patient in a particular block, a matched person in terms of the abovementioned variables would be placed in that block. Then, these two patients in a given block would be randomly assigned to the intervention and control groups. To do randomization, an identification code will be given to each eligible patient in each block, and then, the code of patients with the same age, BMI, and medication will be stated in the lottery container. A person who will be unaware of the study aims will be asked to draw the codes out of the container randomly. The first code will be assigned to the intervention group and the second code to the control group. This will be done for all containers. All patients, researchers, rheumatologists, statistical analysts, and laboratory staff will be blind to the intervention. Random allocation will be done by a third person who is unaware of the aim of our study. Patients in the intervention group (*n* = 20) will receive 30 g/day low-salt and low-fat probiotic cheese. Participants in the control group (*n* = 20) will receive low-salt and low-fat cheese without probiotics. Packaging of both kinds of cheeses would be in the same shape and color. The intervention will last for 12 weeks. Assessment of primary and secondary outcome variables will be done at the study baseline and end of the trial. A standard container will be given to participants, and they will be asked to that container to make sure they are consuming the specified amount. Participants will be asked not to change their lifestyle, dietary habits, and medicines throughout the study. To assess dietary intakes throughout the study, we will fill four 1-day 24-h dietary recalls (including two working days and two non-working days) once every 3 weeks by telephone interview. To complete dietary recalls, participants will be asked to report dietary intakes based on household measures. Then, we will convert the reported amounts to grams using available booklets. The average dietary intakes in these 3 days will be considered as participants’ mean dietary intakes throughout the intervention. To obtain nutrient intakes based on these food recalls, we will use the Nutritionist IV software (based on US National Nutrient Databank) modified for Iranian foods. In addition, four 1-day physical activity records (including two working days and two holidays) will be completed from all patients at weeks 3, 6, 9, and 12 of intervention to assess physical activity during the study. Participants will be requested to report all activities they have during a specific day with the name and type of activity as well as the time spent. All participants will be educated on how to record their activities throughout the study before the start of the trial. Furthermore, patients in both groups will be asked not to change their physical activity throughout the trial.

**Fig. 2 Fig2:**
[figure not shown]
Standard Protocol Items: Recommendations for Interventional Trials (SPIRIT) chart of the enrollments and assessments during randomized controlled trials

### Adherence

To determine the adherence to the intervention, individuals will be asked to record their daily consumption of cheese in a checklist given to them by the investigators. To increase compliance and avoid forgetting the use of cheese, participants will receive short messages on their cellphones every day as reminders. We also ask patients to deliver empty packages of cheese.

### Adverse events

We will ask the patients to report any adverse events that may have occurred during the study. These events will be recorded by investigators. If a given trial participant will complain about any rare harmful effect of the intervention or will want to quit the study based on personal reasons, we will exclude her/him from our trial.

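### Patients excluded for events after randomisation are either dropped, against the stated intention-to-treat approach, or kept with a change fixed at zero

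*Protocol article*

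**What the plan says.** All references are to the protocol article.

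- **Participants.** Entry conditions come first, including no antibiotics or supplements in the preceding 3 months. A second list then covers the study period: "The exclusion criteria would be any alteration in the type or dosage of medicines during the intervention, taking dietary supplements or antibiotics". It goes on to smoking, alcohol and pregnancy, and the next sentence adds whole-day fasting.
- **Adverse events.** Patients are asked to report events, and "These events will be recorded by investigators". Should a participant "complain about any rare harmful effect of the intervention or will want to quit the study based on personal reasons, we will exclude" that person from the trial.
- **Study design and intervention.** "Assessment of primary and secondary outcome variables will be done at the study baseline and end of the trial". The intervention lasts 12 weeks.
- **Statistical analysis.** The principle is stated first: "To handle non-adherence, we will use the intention-to-treat approach for data analysis". The method for gaps in the data is then named: "Missing values will be dealt with using the last observation carried forward (LOCF) method".

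The article does not say that an excluded patient is still measured at week 12, or that she stays in the analysis set.

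**The concern.** Each of these exclusions is triggered by something that happens after randomisation. Several triggers could plausibly be influenced by the allocated cheese or by the course of the arthritis: a dose change because the disease flares or improves, an antibiotic for an infection, a complaint about the product. Removing patients for such reasons can leave two groups that are no longer comparable, even though they were formed at random from matched pairs.

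The analysis section invokes intention-to-treat specifically for non-adherence. A patient who takes a supplement or an antibiotic, or stops the cheese because it disagrees with her, is the kind of departure that principle should absorb. The conduct rules remove her instead, and no analysis plan can recover a week-12 sample that was never drawn.

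There is also a consequence for harms. A reported event is recorded, but if the patient then leaves the trial, its course and any later event go unobserved. The trial enrols women on "conventional medications (methotrexate, prednisolone, hydroxychloroquine, sulfasalazine"), so medicine changes and infections are foreseeable events in this population.

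**Working it through.** **Step 1: do the rules act after randomisation?** Yes. Prior antibiotic and supplement use is handled separately as an entry condition. The second list refers to the intervention period and the study period, and the Adverse events rule refers to trial participants.

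**Step 2: what value does an excluded patient contribute?** Outcomes exist at two times, baseline (Y0) and week 12 (Y12). If she is excluded before week 12, there are two possibilities.

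- *Left out.* She was randomised but not analysed, so the analysis is not intention-to-treat.
- *Kept by carry-forward.* The last observation is baseline, so the imputed change is Y0 − Y0 = 0, whatever happened to her.

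**Step 3: what error does each route produce?** In one arm, let p be the fraction excluded, m_k the mean change in those kept and m_e the mean change that those excluded would have shown. The arm's true mean change is (1 − p)·m_k + p·m_e.

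- Left out: the estimate is m_k, so the error is p·(m_k − m_e).
- Carry-forward: the estimate is (1 − p)·m_k, so the error is −p·m_e.

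The between-arm bias is the difference of these errors. It vanishes only if the error is the same in both arms. The documents give no values for p or m_e, so neither the size nor the sign of the bias can be computed.

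**Step 4: illustration on the power scale.** The inputs are from Study sample size calculation: difference 5.71, SD 5.93, two-sided alpha 0.05, power 80%.

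The plan's own figure: n = 2 × (1.96 + 0.85)² × 5.93² / 5.71² = 2 × 7.8961 × 35.1649 / 32.6041 = 17.03, stated as 17 per group. It reproduces.

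Power by the normal approximation is Φ(D / (5.93 × √(2/n)) − 1.96), where D is the expected difference. Assume that a fraction of 10% or 20% is excluded in each arm. The 20% borrows the plan's total drop-out allowance; it is not an estimate of these exclusions.

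| Scenario | n per arm | D | Power |
|---|---|---|---|
| All followed, full effect | 20 | 5.71 | 86.1% |
| 10% left out | 18 | 5.71 | 82.3% |
| 20% left out | 16 | 5.71 | 77.7% |
| 10% carried forward | 20 | 0.9 × 5.71 = 5.139 | 78.2% |
| 20% carried forward | 20 | 0.8 × 5.71 = 4.568 | 68.3% |

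Worked for the last row: 5.93 × √(2/20) = 1.875; 4.568 / 1.875 = 2.436; 2.436 − 1.96 = 0.476; Φ(0.476) = 0.683.

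The table holds the SD at 5.93, takes equal exclusion in both arms and treats exclusion as unrelated to outcome. It therefore shows lost information and dilution only, not the bias of step 3. The contradiction in step 2 does not depend on it.

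**The case against.** The strongest reply is that the sections fit together. Exclusion may mean only that the patient stops the intervention; intention-to-treat keeps her in her arm, and carry-forward supplies the missing value. The article never says outright that follow-up stops, and it refers to the registry for complete protocol details, where procedures after discontinuation might be set out.

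Part of this stands. That follow-up ends is the plain meaning of excluding someone from the trial, not an explicit statement. But the reading does not remove the problem: with one post-baseline assessment, carry-forward can only copy baseline. Nor is the point a missing detail, because the exclusion rules are stated in the article and it is those rules that clash with its analysis principle.

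Three other limits are fair. The harm trigger is a rare harmful effect of the intervention, not every adverse event. A patient's own wish to quit legitimately ends participation. The number of patients affected is unknown.

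A reader might go further and infer that reported harms vanish from the record, or that the rules conceal infections caused by the cheese. The documents do not support either. Reported events are recorded by investigators. The Discussion's remark on infection concerns corticosteroids and NSAIDs, and the Background's concerns high-dose or unregulated probiotic use. The section on interim analyses states that earlier studies found no adverse effect of probiotic cheese. What may be lost is the later course of an event, not the report itself.

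**Conclusion.** The point holds for all the post-randomisation exclusions, not only those for antibiotics or harms. Followed as written, they lead either to an analysis that is not intention-to-treat or to an imputed change of exactly zero for each excluded patient. The conclusion rests on reading exclusion from the trial as the end of follow-up, and on week 12 being the only post-baseline outcome assessment.

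The comparison can be biased if the triggers differ by arm or relate to outcome, but nothing in the documents shows that it will be, or in which direction. In a trial of 40, each excluded patient is 1 of 20 in her arm (5%), so a handful matters. This is a correction worth making before the trial runs, not evidence that the trial cannot answer its question.

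**What to change.** 1. In Participants and Adverse events, reclassify every event arising after randomisation (medicine change, supplements, antibiotics, smoking, alcohol, pregnancy, whole-day fasting, complaint of harm) as a reason to stop the cheese where needed, or as a recorded protocol deviation. None should be an exclusion from the trial. Only withdrawal of consent ends follow-up.
2. Take the planned week-12 blood sample, DAS-28 and HAQ-DI from every randomised patient who still consents.
3. Analyse all of them in their randomised arm, and report harms by arm for all randomised patients.
4. Add a sensitivity analysis without patients who took antibiotics or changed medicines. Keep it secondary, because it is itself selected on events after randomisation.

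The cost is small. The week-12 visit is already planned for all 40 patients, so the extra work is limited to the few who would have been excluded. The drawback is some noise in hs-CRP when the sample follows an infection; the sensitivity analysis shows how far that affects the result.
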